### Assignment of interventions for blinding

The study is a single-blind trial in which the patients will be blinded to their grouping. However, the surgeon will provide the corresponding surgical treatments according to the grouping of patients. After patients are discharged from the hospital, clinicians will send the surgical methods in the form of medical records through the Email.

### Data collection

Clinical data of enrolled patients will require collection through a case report form (CRF) and the electronic data capture (EDC) system. Every month, clinical research associates (CRAs) monitor the electronic database to guarantee data quality when the clinical research coordinator (CRC) enters the clinical data into the EDC system from the CRF.

The CRF includes the following data: (1) Demographic information: sex, age, body mass index, concomitant disease, and medication use; (2) Perioperative laboratory examination: results of routine blood tests, biochemical tests, serum CRP test, PCT, IL-6, and arterial blood gas tests; (3) Auxiliary examination: all enrolled patients will undergo abdominal enhanced CT scans; (4) Surgery data: operation date, operation time, number of operations, blood loss, surgical methods, and intraoperative complications; and (5) Postoperative recovery outcomes: hospital stay, length of ICU stay, organ dysfunction, perioperative blood pressure, and heart rate, hospitalization cost, short-term and long-term postoperative complications, and death (Table 3).

**Table 3 Tab3:** Checklist for the collection of necessary clinical data and follow-up scheme for enrolled patients with IPN

	Baseline		Post-operation				Follow-up					
	Pre-operation	Operation	POD 1	POD 3	POD 7	POD 30	3 months	6 months	9 months	12 months	18 months	24 months
Inclusion/exclusion criteria	×											
Informed consent	×											
Allocation	×											
Demographic information	×											
Laboratory examination	×		×	×	×	×	×	×	×	×	×	×
Auxiliary examination	×						×	×	×	×	×	×
Surgical data		×										
Postoperative recovery outcomes			×	×	×	×						
Physical examination	×						×	×	×	×	×	×

× indicates the need to collect clinical data

POD, postoperative day

The important privacy information of patients will be replaced with statistical codes or numbers, then CRC will transfer the data from CRFs to the EDC system (https://edc.trialdata.cn/Member/Login), and all clinical data will be analyzed anonymously via the EDC system. Detailed results will be openly shared with the permission of the corresponding author at the end of the study.

### Follow-up

After the procedure, a full-time staff member will be responsible for the follow-up of the enrolled patients. Each patient will be followed up for two years after discharge by outpatient or inpatient review, telephone, or mail. Patients will be followed up every three months in the first year after surgery and every six months over the second year after surgery. During the follow-up period, patients are required to undergo physical examinations, abdominal CT scans, and laboratory tests. In addition, researchers will monitor for related clinical symptoms, such as abdominal pain, bloating, and fatty diarrhea. Physical examination will be conducted mainly to check for postoperative incisional hernia. Abdominal CT scan will primarily focus on the morphological changes of the pancreas and blood vessels in the abdominal cavity. Laboratory tests will include routine blood tests and blood biochemistry tests, which are concerned with white blood cells, thrombocytes, blood glucose, blood triglycerides, and glycosylated hemoglobin. The detailed follow-up schedule is shown in Table 3.

### Adverse events

All serious adverse events (SAEs) occurring between the signing of the informed consent and the end of the trial will be recorded in detail within 24 h. Subsequently, researchers will report the SAEs to the ethics committee of the unit. SAEs are defined as any damage whether associated with the anticipative outcome of the surgery or not. The study includes a data monitoring committee that will supervise the safety data in an unblinded manner in accordance with the Standard Operation Procedures for Clinical Trials. Enrolled patients will receive the best treatment available to resolve any complications.

If the incidence of treatment-related deaths or the proportion of Grade IV postoperative complications determined to be causally related to the procedure exceeds 5% of the total number of patients enrolled, the enrollment of patients must be suspended immediately. Continuation of the study will then be subject to review by the Efficacy and Safety Evaluation Committee of the research group.

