### Primary outcome

The primary outcome is the composite endpoint, which consists of mortality and severe complications (Clavien-Dindo ≥ IIIa). According to the Clavien-Dindo classification, postoperative complications classified as higher than Grade IIIa will be regarded as clinically significant (Table 1) [9].

**Table 1 Tab1:** Clavien-Dindo Classification

Grade	Definition
I	Any complication that deviates from the natural course after surgery, including the use of antiemetics, antipyretics, analgesics, diuretics, infusion, and physical therapy, as well as bedside debridement of incision infection
II	Medications other than those permitted for grade I complications are required, including blood transfusion and total parenteral nutrition support
*III*	Surgical, endoscopic, and radiotherapy are required
IIIa	No general anesthesia is required
IIIb	Need for general anesthesia
*IV*	Life-threatening complication, including centeral nervous system complications and required intermittent monitoring or intensive care unit (ICU) treatment
IVa	Single organ dysfunction
IVb	Multi-organ dysfunction
V	Death

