### Monitoring and quality assurance

The study entails a Data and Safety Monitoring Committee (DSMC) and committee members have a clear division of labor and cooperation. The supervision committee consists of a senior professor in the field of gastrointestinal surgery, data managers, data inspectors, medical ethics experts, and methodological teams. The DSMC will have unrestricted access to all research data and have the right to use monitors and auditors’ reports, as well as all other records related to quality assurance activities. The DSMC will periodically review the clinical efficacy and safety data collected in this study and evaluate the accumulated reports of SAEs. Concurrently, it can also implement emergency reviews and evaluations of safety-related issues. The study has a standard operation procedure (SOP) to ensure homogeneity of clinical data. Meanwhile, specialists are responsible for data collection and entry, data cleaning, and follow-up. After all the data are archived, researchers will submit data to the methodology team for statistical analysis. The DSMC is independent of the study sponsors, and there are no conflicts of interest.

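### The SAE definition sets no seriousness threshold, so SAEs are not distinguished from other adverse events and the proportion of patients with an SAE becomes a weak comparison between arms

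*Protocol article*

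**What the plan says.** The Adverse events section of the protocol article gives the definition: "SAEs are defined as any damage whether associated with the anticipative outcome of the surgery or not". It attaches two duties. The first is a 24-hour deadline for recording each SAE, which applies from consent until the trial ends. The second is a reporting route: "researchers will report the SAEs to the ethics committee of the unit".

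Under Monitoring and quality assurance, SAE reports are a named input to the data and safety monitoring committee (DSMC): "The DSMC will periodically review the clinical efficacy and safety data collected in this study and evaluate the accumulated reports of SAEs". The same section adds that "The DSMC will have unrestricted access to all research data".

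Severity is handled elsewhere. Under Primary outcome, the composite is death or a complication of Clavien-Dindo grade IIIa or above. Table 1 there begins with grade I: "Any complication that deviates from the natural course after surgery, including the use of antiemetics, antipyretics, analgesics". The Statistical analyses section plans a chi-square or Fisher's exact test for adverse events.

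**The concern.** The defining sentence says that an event counts whether or not it belongs to the expected result of surgery. That settles relatedness or expectedness. It does not say what makes an event serious: there is no reference to death, threat to life, hospital admission, disability or anything comparable. The word serious therefore does no work, and an SAE is the same thing as an adverse event.

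This is a rule that the article states, not a detail that it leaves to a fuller document. Two things are at stake:

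- **Reporting.** Minor events fall under the same 24-hour recording and ethics reporting as deaths, from consent to the end of the trial. The ethics route has no filter other than this definition.
- **Comparison of arms.** If many patients in both arms have some minor event, the proportion with at least one SAE is pulled towards 100% in both. A given difference in severe events then appears as a much smaller difference in SAE incidence, both in the reports that the DSMC evaluates and in any chi-square or Fisher test of SAEs.

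**Working it through.** **1. Text check.** Under the definition as written, compare three events using Table 1:

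| Event | Clavien-Dindo grade | In the primary endpoint? | SAE as defined? |
|---|---|---|---|
| Fever treated with an antipyretic | I | No | Yes, if counted as damage |
| Incision infection debrided at the bedside | I | No | Yes |
| Fatal haemorrhage | V | Yes | Yes |

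The endpoint separates these events and the SAE definition does not.

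**2. Reproducing the plan's own figure.** Inputs from the Sample size section: 20% (One-step), 45% (Step-up), one-sided α = 0.05, power 80%, withdrawal 20%. With p̄ = 0.325 and d = 0.25:

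n = [1.645·√(2·0.325·0.675) + 0.842·√(0.20·0.80 + 0.45·0.55)]² / 0.25², rounded up to 43 per arm.

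With the continuity correction this becomes 51 per arm. Then 51/(1 − 0.20) = 63.75, so 64 per arm and 128 in total, as stated. The design inputs can therefore be used below.

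**3. Dilution of the SAE proportion.** Assumptions, none of them given by the documents:

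- composite events, at the planned 20% and 45%, stand in for serious events;
- a further share b of patients in each arm has some non-serious event, independently of the composite;
- the arms are compared on patients with at least one SAE, two-sided at 0.05, with all 64 per arm.

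Then p₁ = 1 − 0.80(1 − b), p₂ = 1 − 0.55(1 − b), and p₂ − p₁ = 0.25(1 − b). The difference shrinks in direct proportion to 1 − b. With p̄ the mean of p₁ and p₂, approximate power is

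Φ{[(p₂ − p₁) − 1.96·√(2p̄(1 − p̄)/64)] / √[(p₁(1 − p₁) + p₂(1 − p₂))/64]}.

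For b = 0.4: p₁ = 1 − 0.80 × 0.6 = 0.52 and p₂ = 1 − 0.55 × 0.6 = 0.67, a difference of 0.15.

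| b (assumed) | One-step | Step-up | Difference (points) | Power, approx. | Power, Fisher exact |
|---|---|---|---|---|---|
| 0 | 20% | 45% | 25 | 86.4% | 82.1% |
| 0.2 | 36% | 56% | 20 | 62.4% | 55.2% |
| 0.4 | 52% | 67% | 15 | 40.7% | 35.5% |
| 0.6 | 68% | 78% | 10 | 24.5% | 18.7% |
| 0.8 | 84% | 89% | 5 | 12.8% | 8.3% |
| 0.9 | 92% | 94.5% | 2.5 | 8.1% | 3.5% |

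The loss is substantial well before nearly every patient has an event.

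**4. If events were counted instead.** Under a Poisson model with assumed means of 2 v 3 events per patient, z = 1/√(5/64) = 3.58 and power is about 95%. With 2 v 2.5, z = 0.5/√(4.5/64) = 1.89 and power is about 47%. Counts can still separate the arms, although the Statistical analyses section names no count analysis for adverse events.

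**5. What does not use the definition.** The suspension rule reads "If the incidence of treatment-related deaths or the proportion of Grade IV postoperative complications determined to be causally related to the procedure exceeds 5" percent of patients enrolled. It rests on deaths and Grade IV events (5% of 128 is 6.4, so 7 patients at full enrolment). The interim analysis at 64 patients is of the primary endpoint. Neither calls on the SAE definition.

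**The case against.** The strongest case on the other side is that this is a loose sentence with little consequence. The term defined is still serious adverse events, and that damage takes in a treated fever is an inference. The Adverse events section refers to standard operating procedures, and Trial status says that an SOP and a case report form exist. Working criteria may sit there. This softens the point but does not remove it, because the article states a definition and that definition has no threshold.

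Other objections stand and limit the point. A reader might infer that the SAE data could not separate the arms at all, or that an excess of serious harm would be hidden. The documents do not support either:

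- The DSMC has access to all the data and reviews efficacy and safety data beyond SAE reports. Deaths, organ dysfunction, ICU stay and complications are collected as separate items under Data collection. A fatal haemorrhage remains visible as a death and as a primary-endpoint event.
- Near-zero separation needs close to 100% SAE incidence in both arms. No document gives such a rate.

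A reader might also link the definition to the interim rule, which suspends the trial if the efficacy or safety of One-step is lower. That section specifies analysis of the primary endpoint and does not say that safety means SAE incidence, so the link is not established.

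**Conclusion.** The point holds as a defect in a stated rule. The SAE definition lacks a seriousness threshold, so non-serious events enter 24-hour recording, ethics reporting and the DSMC's SAE review, and the proportion of patients with an SAE is a weak comparison between arms.

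The size depends on b, which is unknown. Power falls by more than half at b = 0.4 and to about 8% at b = 0.9. These figures assume independence, the same b in both arms, and a comparison of patients with at least one event. The 86% at b = 0 is a benchmark based on the composite, not a forecast for a corrected SAE definition.

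The primary endpoint, the sample size, the 5% suspension rule and the interim analysis of the primary endpoint are unaffected. The correction is worth making because it is cheap and the ethics reporting route depends on it.

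**What to change.** Replace the defining sentence with one to this effect: an SAE is any untoward event from consent to the end of the trial, whether or not related to the procedure or expected from it, that results in death, is life-threatening, requires or prolongs hospital admission, causes lasting disability or incapacity, or is otherwise medically important.

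Then:

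- record the Clavien-Dindo grade as a separate severity field, not as a criterion for seriousness;
- state that a protocol-planned procedure, such as Step-up debridement after percutaneous drainage, is not in itself an SAE, since otherwise the tally would follow the assigned strategy;
- record all other events as non-serious adverse events, and report both classes by arm to the DSMC.

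If the SOP already holds such criteria, bring the protocol sentence into line with it. The cost is a short amendment, revised form wording and reclassification of events already reported. Expedited reporting work should fall. No treatment, endpoint or sample size changes.

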### Monitoring and quality assurance

The study entails a Data and Safety Monitoring Committee (DSMC) and committee members have a clear division of labor and cooperation. The supervision committee consists of a senior professor in the field of gastrointestinal surgery, data managers, data inspectors, medical ethics experts, and methodological teams. The DSMC will have unrestricted access to all research data and have the right to use monitors and auditors’ reports, as well as all other records related to quality assurance activities. The DSMC will periodically review the clinical efficacy and safety data collected in this study and evaluate the accumulated reports of SAEs. Concurrently, it can also implement emergency reviews and evaluations of safety-related issues. The study has a standard operation procedure (SOP) to ensure homogeneity of clinical data. Meanwhile, specialists are responsible for data collection and entry, data cleaning, and follow-up. After all the data are archived, researchers will submit data to the methodology team for statistical analysis. The DSMC is independent of the study sponsors, and there are no conflicts of interest.

### Sample size

The sample size was calculated using PASS 11.0 (NCSS Statistical and Data Analysis, USA) software and was estimated based on the results of our center’s previous research and published literature. According to our previous studies and domestic and foreign reports, the incidence of a mixed endpoint is approximately 20% for the “One-step” approach and approximately 45% for the “Step-up” approach [8]. Using a one-sided test, the α value was equal to 0.05, and the statistical power was 80%. The withdrawal rate was expected to be 20% during the study period. Thus, this study requires at least 128 patients, with 64 patients each group.

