**Discussion:**

Compared with the “Step-up,” the “One-step” minimally invasive surgery can significantly reduce the number of operations, reduce the length of hospital stay and hospitalization costs without increasing the incidence of composite endpoint events, and has better short- and long-term efficacy and safety. Additionally, there was no statistically significant difference in perioperative complications and mortality between “Step-up” and “One-step”. This study will assist with the formulation of an effective and scientific “One-step” minimally invasive treatment strategy for IPN, and an understanding of this technique will facilitate clinical decision-making for IPN.

*Trial Registration* ChiCTR2100044348. Trial status: Ongoing.

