#### Allocation concealment mechanism

Patients will be randomly assigned to the experimental group (One-step approach) and the control group (Step-up approach) at a ratio of 1:1 using the block randomization method.

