### Statistical analyses

The results of this trial for primary outcomes will be analyzed based on both the intention-to-treat protocol and per-protocol datasets. SAS 9.2 software (SAS Institute Inc.) was used to generate the randomization sequence. Statistical analyses will be performed with SPSS 21.0 (IBM Corp., Armonk, NY, USA) statistical software. The continuous variables with normal distributions will be described as mean ± standard deviation, and an independent sample *t-test* will be used for difference tests. The continuous variables with non-normal distributions will be described by the median (IQR), and the Mann–Whitney U test will be used for the difference tests. The Chi-square test or Fisher’s exact test will be used for categorical data. The Chi-square test or Fisher’s exact test will be used to assess adverse events. The Kaplan–Meier method will be used to calculate survival analysis. The log-rank test will be used to compare the complication rate between the two groups, and *P* values < 0.05 will be considered statistically significant.

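### The trial is sized on a one-sided 5% test but the analysis section does not state a side, and the abstract already claims no increase in the composite without a margin

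*Protocol article*

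**What the plan says.** The Sample size section of the protocol article sets the design: "Using a one-sided test, the α value was equal to 0.05, and the statistical power was 80" per cent. The assumed rates are that "the incidence of a mixed endpoint is approximately 20% for the “One-step” approach and approximately 45% for the “Step-up” approach". It adds "The withdrawal rate was expected to be 20% during the study period" and concludes "Thus, this study requires at least 128 patients, with 64 patients each group".

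The Statistical analyses section assigns the chi-square or Fisher's exact test to categorical data. It says the primary outcome will be analysed on both intention-to-treat and per-protocol sets, and that P values below "0.05 will be considered statistically significant". It does not mention a side.

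The Discussion part of the abstract says One-step reduces operations, stay and costs "without increasing the incidence of composite endpoint events". It adds that "there was no statistically significant difference in perioperative complications and mortality between" the two approaches. The same part of the abstract gives the trial status as ongoing. The article states no non-inferiority margin.

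**The concern.** The assumed rates describe superiority of One-step, and the one-sided 5% level determines the sample size. If the final P value is read from standard chi-square or Fisher output and compared with 0.05, the test has a nominal 2.5% in the favourable direction, not the 5% used for sizing. The choice between the two readings could then be made after the result is known.

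The abstract adds a separate problem. Saying that the composite is not increased is a non-inferiority conclusion. A trial sized to detect a 25-point reduction has no margin for that conclusion and cannot reach it from a non-significant difference. If the wording stays, a null result could be published as reassurance about safety.

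**Working it through.** **Inputs.** From the Sample size section: p1 = 0.45 (Step-up), p2 = 0.20 (One-step), difference d = 0.25, one-sided α = 0.05, power 80%, withdrawal 20%. Allocation is "at a ratio of 1:1 using the block randomization method". The mean rate is 0.325.

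**1. Reproduce 128.** For two proportions with pooled variance under the null,

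n = [z_α √(2 × 0.325 × 0.675) + z_β √(0.45 × 0.55 + 0.20 × 0.80)]² / d²

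The two roots are 0.6624 and 0.6384. With z_α = 1.645 and z_β = 0.842, n = 42.3, that is 43 per arm. The continuity correction, n_c = (n/4)[1 + √(1 + 4/(n d))]², gives 50.02, rounded up to 51. Then 51 / 0.8 = 63.75, so 64 per arm and 128 in total. The stated figure is reproduced exactly, and it depends on the one-sided level.

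**2. Same inputs, two-sided 5%** (z_α = 1.960).

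| Formula | Per arm, evaluable | Per arm after 20% loss | Total |
|---|---|---|---|
| Uncorrected | 54 | 68 | 136 |
| Continuity-corrected | 62 | 78 | 156 |

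**3. Power of the planned size at 45% v 20%** (exact binomial enumeration).

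| Evaluable per arm | Test | One-sided 5% | Two-sided 5% |
|---|---|---|---|
| 51 | Pearson | 86.9% | 78.3% |
| 51 | Fisher | 81.9% | 71.9% |
| 64 | Pearson | 92.7% | 86.9% |
| 64 | Fisher | 89.8% | 82.1% |

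Under the design rates, the chance that the two readings disagree with a Pearson test is 86.9 − 78.3 = 8.6 points at 51 per arm, and 92.7 − 86.9 = 5.8 points at 64.

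**4. A result on which they disagree.** Take 19/64 events on One-step and 29/64 on Step-up (30% v 45%). The pooled rate is 48/128 = 0.375, and z = (10/64) / √(0.375 × 0.625 × 2/64) = 1.826. The one-sided P is 0.034 and the two-sided P is 0.068. The first is significant at 0.05 and the second is not.

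**5. What a non-significant difference can exclude.** With equal true rates p, the 95% CI half-width is 1.96 √(2p(1 − p)/n).

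| p in both arms | n = 64 per arm | n = 51 per arm |
|---|---|---|
| 20% | 13.9 points | 15.5 points |
| 45% | 17.2 points | 19.3 points |

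Suppose One-step were truly 10 points worse. This is an assumption, taken over 30% v 20% up to 45% v 35%. At 64 per arm a two-sided 5% test would be non-significant 74–78% of the time (Pearson) or 80–83% (Fisher).

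**6. Size for a non-inferiority claim.** The article gives no margin, so these are illustrations only, at one-sided 5% and 80% power: n = 2p(1 − p)(1.645 + 0.842)² / margin². A 10-point margin needs 198 per arm (both rates 20%) to 307 (both 45%). A 15-point margin needs 88 to 137. All exceed 64.

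**The case against.** The strongest reply is that the article does not contain competing hypotheses. The Sample size section is the only place that states a side. The analysis section is silent, which is not the same as saying two-sided, and a full protocol or analysis plan may settle it. The two-sided reading rests on how these tests are normally reported. That stands, so this part is a gap between two sections and not a contradiction. A reader might infer that the hypothesis is stated in three conflicting ways; the text does not go that far.

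The abstract is prose, not a formal hypothesis. Its sentence on no significant difference names perioperative complications and mortality, not the composite, and the same paragraph also claims better efficacy and safety. That stands too. The phrase about not increasing events does name the composite, however, and no analysis plan could make results of an ongoing trial valid or supply the missing margin in published text.

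The power shortfall is modest. With every randomised patient analysed, as intention-to-treat implies, either test exceeds 80% two-sided. Only after the assumed 20% loss does it fall short, by about 2 points with Pearson.

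It is also tempting to say that a one-sided test for benefit conflicts with the Interim analyses section, which suspends the trial if One-step does worse. That section names no significance test, and a monitoring rule for harm can stand beside a one-sided efficacy test. The documents do not support that argument.

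**Conclusion.** The point holds in a limited form. The one-sided 5% level that produces 128 is not carried into the analysis section, so significance is undetermined when the one-sided P lies between 0.025 and 0.05. On the two-sided reading, power after the planned loss is 78% (Pearson) or 72% (Fisher) against a stated 80%; without loss it is 87% or 82%. The false-positive rate in favour of One-step is nominally 5% on one reading and 2.5% on the other. Exact rates depend on the test and, for Fisher, are lower.

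The abstract's claim about the composite does not match the powered hypothesis, has no margin, and is worded as a finding before the trial has one. With half-widths of about 14–17 points at 64 per arm, a non-significant difference would not exclude a material increase.

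A reader might infer that the sample size is wrong. It is not: 128 is right for the test it states.

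These figures rest on the article's rates of 45% and 20%, on 51 evaluable patients per arm after 20% loss, and on chi-square and Fisher P values being two-sided as usually reported. The change should be made, but the trial is not unsound without it.

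**What to change.** 1. State the same side and alpha for the primary test in the Sample size and Statistical analyses sections. A two-sided 5% Pearson chi-square on all randomised patients, with the risk difference and its 95% CI, is preferable. Carrying the one-sided 5% into the analysis section would also remove the ambiguity; choosing two-sided is a matter of convention and of a stricter error rate.
2. If two-sided is chosen, keep 128 and restate power as about 87% with all patients analysed and about 78% after 20% loss, saying openly that the second figure is below the 80% target.
3. Remove the statements worded as results from the Discussion part of the abstract.
4. State that a non-significant difference will not be reported as no increase in the composite unless the upper confidence limit for One-step minus Step-up lies below a margin fixed in advance.

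The cost is wording and a stricter criterion, with no more patients if the shortfall after loss is accepted. Holding 80% two-sided after 20% loss would need 136 patients (uncorrected) to 156 (continuity-corrected), that is 8 to 28 more.
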